##### Secondary endpoints:

##### Proportion of subjects with an ACR20 and ACR70 at Week 14

The endpoints, ACR20 and ACR70 at Week 14, will be analyzed using a chi-square test, Fisher's exact test, or logistic regression with treatment group as a term in the model, as appropriate.

##### Change from baseline in Quality of Life (HAQ-DI, SF-36, FACIT-F) at Week 14

Change from baseline for HAQ-DI, FACIT-F scores, and SF-36 scores (mental and physical health components) will be analyzed using an analysis of covariance with treatment group and baseline as terms in the model. If the data are not normally distributed, a nonparametric analysis of covariance will be performed.

##### Change from baseline disease activity score (DAS28) at Week 14

The DAS28 score is a measure of the subject's disease activity and is calculated as follows:

$$\text{DAS28} = 0.56 * \text{sqrt}(\text{TJC } 28) + 0.28 * \text{sqrt}(\text{SJC } 28) + 0.70 * \ln(\text{ESR}) + 0.014 * \text{GH}$$

(TJC = tender joint count; SJC = swollen joint count; ESR = erythrocyte sedimentation rate; GH = subject's global assessment)

and/or

$$\text{DAS28} = 0.56 * \text{sqrt}(\text{TJC } 28) + 0.28 * \text{sqrt}(\text{SJC } 28) + 0.36 * \ln(\text{CRP}+1) + 0.014 * \text{GH} + 0.96$$

Change from baseline disease activity score (DAS28) will be analyzed using an analysis of covariance with treatment group and baseline as terms in the model. If the data are not normally distributed, a nonparametric analysis of covariance will be performed.

##### Proportion of subjects with a categorical DAS28 EULAR response at Week 14

The EULAR response categories of good, moderate, and no response are defined as shown in Table 16-1 below.

**Table 16-1. EULAR Criteria of Response**

| Post-Baseline
DAS28 Attained | Decrease (Improvement) in DAS28 From Baseline |                   |             |
|---------------------------------|-----------------------------------------------|-------------------|-------------|
|                                 | >1.2                                          | ≤1.2 and ≥0.6     | <0.6        |
| <3.2                            | Good Response                                 | Moderate Response | No Response |
| ≥3.2 and ≤5.1                   | Moderate Response                             | Moderate Response | No Response |
| >5.1                            | Moderate Response                             | No Response       | No Response |

The proportion of subjects with a EULAR response at Week 14 will be analyzed using a chi-square test, Fisher's exact test, or logistic regression with treatment group as a term in the model, as appropriate.

#### Changes from baseline in the individual ACR core set parameters at Week 14

Summary statistics of change from baseline in the individual ACR core set parameters will be presented.

#### Exploratory endpoints:

##### ACR responses over time (including ACRn)

To achieve an ACRn response, a n% improvement compared to baseline is required for both swollen and tender joint counts, as well as 3 out of 5 additional parameters: subject's global assessment of disease activity, Investigator's global assessment of disease activity, subject's assessment of pain, HAQ-DI, and hsCRP or ESR.

Summary statistics of ACR responses over time (including ACRn) will be presented.

##### Change in Sjogrens assessments

Summary statistics of subject-reported dryness including VAS (ocular, vaginal, skin, and oral) and OSDI will be presented for subjects with Sjogrens syndrome.

#### Other analyses:

##### Rheumatoid arthritis disease markers

Summary statistics of markers of disease activity will be presented.

## **16.2.5 Safety Data**

### **16.2.5.1 Analysis Population**

The safety population will be defined as all subjects who received at least one dose of study treatment.

### **16.2.5.2 Methods of Analysis**

All AEs, laboratory abnormalities, ECG, vital signs, and physical examinations will be evaluated for safety.

#### *Clinical Adverse Events*

Only treatment-emergent AEs will be presented in the summary tables. Treatment-emergent is defined as having onset date that is on or after start of study treatment, or that is worsened after the start of study treatment.

Incidence of treatment-emergent AEs will be summarized by treatment groups, overall, by severity, and by relationship to study treatment. The summary tables will include incidence estimates for overall system organ class as well as for preferred terms within each system organ class.

#### *Laboratory Data*

Laboratory data will be summarized using shift tables. Shifts from baseline to high/low status for hematology, coagulation, and blood chemistry, and shifts from baseline to high/positive status for urinalysis will be presented. In addition, the shift from baseline to the maximum post-baseline value and the shift from baseline to the minimum post-baseline status will be presented for each laboratory test by treatment group. Summary statistics may be presented for selected laboratory parameters.

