### **Safety analyses**

The following will be calculated:

- the incidence of all serious adverse events (SAEs),
- the incidence of all AEs,
- the incidence of all infections,
- the proportion of subjects with laboratory assessment values outside the normal range, and
- the proportion of subjects who tested positive for anti-nuclear or tetanus antibodies.

---

CONFIDENTIAL

The information contained herein may not be used, disclosed, or published without the written consent of  
Biogen Idec Inc.

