#### LABORATORY TESTS

13. Subjects with any laboratory test result at Screening considered clinically significant (as determined by the Investigator) or
  - Aspartate aminotransferase (AST) or alanine aminotransferase (ALT)  $> 1.5$  times than the upper limit of normal (ULN) established by the central laboratory.
  - Platelet count  $< 150,000/\mu\text{L}$
  - Hemoglobin  $< 8.5$  g/dL
  - Neutrophils  $< 1.5 \times 10^3/\mu\text{L}$ .
14. Positive for hepatitis C antibody or hepatitis B [HBsAg, HbcAb, or HBsAb] at Screening.

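### The committed laboratory summaries are ungraded shifts to high/low status, although the entry criteria admit mildly abnormal baselines; graded baseline-by-worst-value tables should be added

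*Protocol*

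**What the plan says.** Protocol section 16.2.5.2 (Laboratory Data) sets the format: "Laboratory data will be summarized using shift tables". For hematology, coagulation and chemistry the categories are high and low: "Shifts from baseline to high/low status for hematology, coagulation, and blood chemistry". It then adds, per test and treatment group, that "the shift from baseline to the maximum post-baseline value and the shift from baseline to the minimum post-baseline status will be presented". The sentence says value for the maximum and status for the minimum, without explaining the difference. On numeric summaries: "Summary statistics may be presented for selected laboratory parameters".

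The Synopsis (Safety analyses) lists one laboratory measure: "the proportion of subjects with laboratory assessment values outside the normal range".

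Section 8.2, criterion 13, opens with "Subjects with any laboratory test result at Screening considered clinically significant (as determined by the Investigator) or" and then gives numeric limits. AST or ALT excludes only above 1.5 "times than the upper limit of normal (ULN) established by the central laboratory". The other limits are "Hemoglobin $< 8.5$ g/dL", neutrophils below 1.5 x 10^3/µL and platelets below 150,000/µL.

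For contrast, Table 16-2 in the same section gives vital signs numeric criteria that, in every row, combine an absolute limit with a change from the pre-dose value.

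**The concern.** A status shift records whether a result crossed a normal limit. It does not record how far, and it records nothing when the subject was already beyond that limit. Both gaps matter here. The entry limits allow some subjects to start above the ULN for transaminases or below the lower limit for hemoglobin. All subjects also take MTX, so small ALT crossings can be expected in every arm and can mask a few large ones.

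The Synopsis measure does not help. It is also binary, and it counts a subject who was abnormal at entry whether or not that subject worsens.

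Safety and tolerability of the five regimens is a secondary objective (section 6.2), and the study is meant to assist dose selection (section 5.3). If the tables were produced exactly as committed, two arms could look alike on shifts while one held several large ALT rises or hemoglobin falls.

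**Working it through.** The plan states no figure on this point, so there is none to reproduce.

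**Step 1: classify example values by status.** High means above the ULN; low means below the lower limit of normal (LLN). The protocol gives no LLN for hemoglobin, so 11.5 to 13.5 g/dL is assumed.

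| Test | Baseline | Worst post-baseline | Status | Counted as a shift? |
|---|---|---|---|---|
| ALT (x ULN) | 0.8 | 1.1 (1.4-fold) | normal to high | yes |
| ALT (x ULN) | 0.8 | 10 (12.5-fold) | normal to high | yes |
| ALT (x ULN) | 1.4 | 10 (7.1-fold) | high to high | no |
| Hemoglobin (g/dL) | 9.0 | 7.0 | low to low, at any assumed LLN | no |

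Both abnormal baselines pass the numeric limits in criterion 13 (1.4 is not above 1.5; 9.0 is not below 8.5).

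**Step 2: check whether another committed laboratory summary shows size.**
- The maximum shift might, if value means the numeric result. If both the maximum and the minimum shift mean status, neither does. The text does not settle this.
- Summary statistics would, through the range, but they are optional.
- The Synopsis proportion would not.

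**Step 3: illustrate how many subjects could be affected.** Every distributional input is an assumption; only the entry limits and the number of draws come from the protocol.

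*ALT.* Assume ALT/ULN is log-normal, with between-subject SD(log) 0.35 and within-subject SD(log) 0.25. The Screening value is at most 1.5, and chemistry is drawn five times after baseline up to Week 14 (Weeks 2, 4, 6, 10 and 14, as scheduled). Suppose 8% of a BG9924 arm has a 5-fold rise. By simulation:

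| Assumed median ALT (x ULN) | High at Day 0 | Share of >3 x ULN cases that start high: rise in all draws | Same share: rise in one draw |
|---|---|---|---|
| 0.5 | 5% | 8% | 13% |
| 0.6 | 11% | 14% | 20% |
| 0.7 | 18% | 21% | 27% |

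At median 0.6, shift-to-high is about 19% on placebo and 24% on BG9924. In 76 subjects that is 0.19 x 76 ≈ 14 against 0.24 x 76 ≈ 18. Values above 3 x ULN occur in about 0% on placebo and in 4% (one draw) to 6% (all draws) on BG9924, or about 0 against 3 to 5 subjects. The status table shows the first contrast and not the second.

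*Hemoglobin.* Assume an LLN of 12 g/dL and a normal distribution with SD 1.3, truncated at 8.5. The share low at entry is [Φ((12 − m)/1.3) − Φ((8.5 − m)/1.3)] / [1 − Φ((8.5 − m)/1.3)]:
- m = 13: (0.2209 − 0.0003)/0.9997 = 22%
- m = 12.5: (0.3503 − 0.0010)/0.9990 = 35%
- m = 12: (0.5000 − 0.0035)/0.9965 = 50%

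These subjects cannot shift down to low. The exclusion for clinically significant results is not modelled, so the ALT and hemoglobin entry shares may be too high.

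**The case against.** Laboratory grades and table layouts usually belong in the SAP, which is not at hand, and nothing in section 16.2.5.2 forbids graded tables. That is right as far as it goes: the absence of grades is not in itself an error, and no figure is wrong. But the protocol does fix a format here, leaves the numeric summaries optional, and sets numeric magnitude-and-change criteria for vital signs in the same section. Improving the stated rule is a fair request.

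A reader might infer that status shifts are the only laboratory analysis and that worsening from an abnormal baseline cannot register at all. The documents do not support that. The maximum shift may use values. An abnormal laboratory finding can be an adverse event (section 15.1.1), and treatment-emergent events include those that worsen and are tabulated by severity. The Safety Assessor reviews laboratory data (section 12.1), and a DMC reviews unblinded safety data quarterly (section 19.2.1).

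These routes are real but incomplete. Section 15.1.1 sets no laboratory threshold, so recording depends on the Investigator. Severity in section 15.3.2 rests on symptoms and function, so a large asymptomatic rise could be graded mild. Sites do not receive lymphocyte counts after Screening (section 9.3), although dose-related lymphocyte effects were noted in earlier studies, so Investigators cannot report those changes from the study results. DMC review does not replace the reported comparison between arms.

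A reader might also want to compare the power of the two tabulations. That would not be apt: section 16.2 plans formal comparisons for efficacy endpoints, safety is summarized descriptively, and every input would be assumed. On the illustration above, most cases above 3 x ULN (73% to 92%) start from a non-high value and do appear as a shift, though without their size.

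**Conclusion.** The point holds as a limitation of the committed summary, not as a contradiction or a wrong figure. On status alone, worsening from an abnormal baseline is not a shift, and trivial and large crossings from a normal baseline count alike. That follows directly from section 16.2.5.2 and criterion 13 and needs no assumption beyond an ordinary hemoglobin reference limit. What would show magnitude is optional, ambiguously worded, or dependent on Investigator judgement.

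The size is not known from the protocol. The shares shown (5% to 18% high for ALT, 22% to 50% low for hemoglobin) only illustrate what assumed distributions would give. The change is worth making because it is cheap and bears on the safety comparison between regimens.

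**What to change.** In section 16.2.5.2:

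1. Keep the shift tables, but cross-tabulate baseline band by worst post-baseline band for each treatment group. Use multiples of the ULN for AST and ALT. For hemoglobin, neutrophils and platelets, use stepped bands that include the protocol's own entry limits (8.5 g/dL, 1.5 x 10^3/µL, 150,000/µL). Treat lymphocytes likewise. Report the number of subjects who worsen by at least one band. The cut-points are for the sponsor to set.
2. State whether the maximum and minimum post-baseline shifts use numeric values or normal-range status, with the same term for both.
3. Make change-from-baseline summaries, including the range, mandatory rather than optional for AST, ALT, hemoglobin, neutrophils, platelets and lymphocytes.

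This affects reporting only and uses central-laboratory data already collected, with no new samples or visits. The cost is longer tables and the need to choose band limits, preferably before unblinding. Lymphocyte tables should be kept from the sites while the blind is in force, as the protocol already requires for the counts.

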#### *Antibody Data*

The proportion of subjects who developed ANA or tetanus antibodies will be summarized.

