**Safety Assessments:**

Physical examinations, vital signs, electrocardiogram (ECG), hematology, lymphocyte and leukocyte subset analysis (CD3+, CD4+, CD8+, CD19+, CD16+, CD56+, and CD14+), blood chemistry, international normalized ratio (INR; for anticoagulant monitoring), prothrombin time (PT), and activated partial thromboplastin time (aPTT), urinalysis, quantitative immunoglobulins (total, IgA, IgG, IgM), tetanus titers, antibodies to BG9924, antinuclear antibodies (ANA), anti-double stranded DNA (anti-dsDNA), and monitoring for infections, adverse events (AEs), and concomitant therapy use.

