The therapeutic rationale for treatment of RA with BG9924 is based on the general mode of action where the quality of immune responses will be dampened by way of a number of mechanisms, notably via altered trafficking through the lymph nodes and abortive germinal center reactions. This view is supported experimentally by results obtained in rodent models of arthritis using a murine homologue (mLT $\beta$ R-Ig). Prophylactic treatment with mLT $\beta$ R-Ig blocked the induction of collagen-induced arthritis (CIA) in mice and adjuvant arthritis in Lewis rats. In mice with established arthritis, mLT $\beta$ R-Ig treatment blocked disease progression, reducing the severity of arthritic symptoms and joint damage. Although the underlying mechanism of action is not understood, reduced cell trafficking into the draining lymph nodes and a potential reduction in the quality of the pathogenic anticollagen II antibodies were noted. Human RA synoviocytes were shown to respond to LT $\beta$ R signaling with chemokine release and increased intracellular adhesion molecule (ICAM) expression, indicating a potentially direct proinflammatory consequence of the LT pathway in the joint. The ongoing Phase 2a clinical study (Study 104-RA-201) has also provided encouraging data, showing significant improvements in both tender and swollen joint counts after 4 weeks of dosing. Therefore, BG9924 is felt to be a promising new therapeutic option for the treatment of RA patients.

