### **11.4 Concomitant Therapy and Procedures**

A concomitant therapy is any drug or substance administered from Screening until the end of the study. This includes any preventative vaccines (e.g., flu vaccines) that the subject may receive during the course of this study. The dose of allowed concomitant therapy may be decreased if required due to toxicity. The dose should not be increased.

A concomitant procedure is any therapeutic intervention (e.g., surgery/biopsy, physical therapy) or diagnostic assessment (e.g., blood gas measurement, bacterial cultures) performed from Screening until the end of the study.

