#### **14.2.2 Visit 1 (Week 0, Day 0)**

- Physical examination

---

CONFIDENTIAL

The information contained herein may not be used, disclosed, or published without the written consent of  
Biogen Idec Inc.

- Vital signs: temperature, heart rate, respiratory rate, and supine blood pressure (after 5 minutes' rest)
- ACR core set measurements (see Section 12.1 for list of measurements)
- QoL (SF-36, FACIT-F)
- Sjogrens Assessments (see Section 12.1 for assessments), if applicable
- Blood samples collected for:
  - hsCRP and ESR (ESR to be performed at local laboratory)
  - RF and anti-CCP-2 antibody
  - RA Disease Markers (serum BAFF, COMP, calgranulin, and MMP3)
  - Quantitative FACS analysis, only in subjects participating in the optional PK sub-study (see Section 12.4 for list of variables)
  - Cytokine panel (see Section 12.4 for list of variables)
  - Serum BG9924 PK concentration
  - Hematology (see Section 13.2 for list of variables)
  - Quantitative Ig (IgA, IgG, and IgM)
  - Blood chemistry (see Section 13.2 for list of variables)
  - INR, PT, and aPTT
  - ANA and anti-dsDNA antibody assays
  - Serum anti-BG9924 antibody assay
  - Tetanus antibody titers
  - RNA Analysis
- Urinalysis (see Section 13.2 for list of variables)
- Urine pregnancy test
- Study treatment administration
- Monitoring of AEs/SAEs (see Section 15.2)
- Monitoring of concomitant therapy

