### **16.4 Sample Size Considerations**

A total of 380 subjects will be randomized at a ratio of 2:2:2:2:1:1 providing 76 subjects per treatment group for every other week dosing and 38 subjects per treatment group for monthly dosing. Assuming 15% dropout, a Type I error rate of 5%, Week 14 ACR50

CONFIDENTIAL

The information contained herein may not be used, disclosed, or published without the written consent of  
Biogen Idec Inc.

responses of a single BG9924 treatment group (42%) and placebo (15%), there is 90% power for a comparison of an every other week BG9924 treatment group versus placebo and 74% power for a comparison of a monthly BG9924 treatment group versus placebo by using Fisher's exact test.

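### Tetanus titers are to be summarised as the proportion who developed antibodies, a measure suited to ANA that does not count reversion to negative or a falling titer

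*Protocol*

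**What the plan says.** Two places in the protocol state an analysis of tetanus antibody, and they differ.

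- Section 16.2.5.2, Antibody Data: "The proportion of subjects who developed ANA or tetanus antibodies will be summarized".
- Section 3 (Synopsis), Safety analyses: "the proportion of subjects who tested positive for anti-nuclear or tetanus antibodies".

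Neither names a visit, a baseline comparison, a change in titer or a cut-off. Both put tetanus in one phrase with ANA.

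The measurement itself is quantitative. The blood samples listed for Visit 1 (Section 14.2.2) include "Tetanus antibody titers", and the same item is listed for Week 14 (Section 14.2.13) and Week 26 (Section 14.2.16). The Synopsis classes it as a safety assessment, in the run "quantitative immunoglobulins (total, IgA, IgG, IgM), tetanus titers, antibodies to BG9924".

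On mechanism, Section 5.1.1 says that "the quality of immune responses will be dampened by way of a number of mechanisms", and names abortive germinal center reactions among them. The schedules in Sections 4 and 14.2 contain no tetanus immunization. Vaccines appear only as concomitant therapy; of that term Section 11.4 says "This includes any preventative vaccines (e.g., flu vaccines) that the subject may receive during the course of this study".

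**The concern.** For ANA the event to watch for is the appearance of antibody. For tetanus, with no immunization in the schedule, appearance is not an expected drug effect. The effect that the protocol's own rationale would suggest is a decline in antibody that the subject already has. One sentence applies the same measure to both, so for tetanus it looks in the wrong direction and sets the titer aside.

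At stake is a safety reading on existing humoral immunity, from samples that the trial already collects. Followed literally, the Section 16 summary would be the same in subjects whose tetanus antibody was stable and in subjects who lost it, provided that all of them were positive at baseline. This is a stated measure that fits its variable badly, not a detail left open for the statistical analysis plan.

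**Working it through.** The protocol gives no figure for tetanus antibody, so there is nothing to reproduce. The check is what each stated measure can register, followed by illustrations on assumed inputs.

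**1. What each measure registers**

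| Event in a subject | Developed (Section 16.2.5.2) | Tested positive (Synopsis), by visit and arm | Tested positive, read as ever positive |
|---|---|---|---|
| Negative to positive | yes | yes | yes |
| Positive to negative | no | yes | no |
| Titer falls, stays above cut-off | no | no | no |

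The Synopsis does not say which of the last two columns is meant.

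**2. Who can count under the Section 16 measure**

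Group sizes come from Section 16.4: "providing 76 subjects per treatment group for every other week dosing and 38 subjects per treatment group for monthly dosing". Placebo has the same allocation share as an every-other-week group, so also 76. Baseline seropositivity *s* is not in the protocol; assume 50% to 95%.

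- Can develop antibody: n × (1 − s). For n = 76: 76 × 0.50 = 38, down to 76 × 0.05 = 3.8. For n = 38: 19 down to 1.9.
- Can lose antibody: n × s. For n = 76: 38 up to 72.2. For n = 38: 19 up to 36.1.

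The second set cannot enter the numerator, whatever happens to the titers.

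**3. How far a proportion positive moves when titers fall**

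Assume log-normal titers with a baseline median 10 times the cut-off and a log10 SD of 0.4 or 0.6. After a fall by a factor *f* in every subject, the proportion positive is Φ((1 − log10 f) / SD).

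| Fall in every subject | SD 0.4 | SD 0.6 |
|---|---|---|
| none | 99% | 95% |
| 2-fold | 96% | 88% |
| 4-fold | 84% | 75% |

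So a halving of every titer moves the Synopsis measure by about 3 to 7 percentage points, and the Section 16 measure not at all among those positive at baseline.

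**4. Power, on assumed inputs (two-sided 5%, 65 per arm)**

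After the 15% dropout assumed in Section 16.4, 76 × 0.85 = 64.6, about 65, and 38 × 0.85 = 32.3, about 32.

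- Proportion positive (normal approximation), 90% seropositive at baseline: 31% power if 10% of positives revert (90% v 81%), and 75% if 20% revert (90% v 72%). At 80% seropositive: 19% and 53%.
- Mean change in log10 titer, 2-fold fall versus placebo: above 99% at an SD of change of 0.2 to 0.3, and 93% at 0.5.

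**5. Detectable geometric mean ratio at 80% power**

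Ratio = 10^(−(1.96 + 0.842) × SD × √(1/n₁ + 1/n₂)), with the SD of log10 change assumed.

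| SD | Every other week, 65 v 65 (root term 0.1754) | Monthly, 32 v 65 (root term 0.2160) |
|---|---|---|
| 0.15 | 0.84 | 0.81 |
| 0.20 | 0.80 | 0.76 |
| 0.30 | 0.71 | 0.66 |

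**The case against.** **The Synopsis measure can show some loss.** This stands. With samples at Day 0 and Week 14, a proportion positive by visit and arm would reveal reversion to negative. A reader might infer that neither wording could ever show loss; the protocol does not support that. What remains is that the Synopsis names no visit, misses a decline above the cut-off, and differs from Section 16.

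**The general laboratory analysis may cover tetanus.** Section 16.2.5.2, Laboratory Data, says "the shift from baseline to the minimum post-baseline status will be presented for each laboratory test by treatment group", and Section 19.1.4 lists tetanus titers among the central laboratory tests. The reading is arguable. Against it, the panels named there are hematology, coagulation, chemistry and urinalysis; antibody data have their own heading; and tetanus is absent from the Section 13.2 list. A general sentence does not clearly override the specific one.

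**Loss of existing antibody is not a stated purpose.** Correct. No section says why titers are drawn. Section 5.1.1 gives a therapeutic rationale, and the warning in Section 14.1 concerns impaired response to infection. That a fall is the safety question is a reasonable inference from these and from the listing beside immunoglobulins, and no more.

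**A result near 0% in every arm is not assured.** Also correct. It would require near-universal seropositivity at baseline, which is not given. An incidental tetanus vaccination is also possible, since Section 11.4.2 bars only live or live attenuated vaccines.

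**Other monitoring exists.** Quantitative immunoglobulins, infection incidence and quarterly unblinded safety review by the data monitoring committee all continue. None of them measures antibody to a specific past immunization.

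**The statistical analysis plan may add titer summaries.** It may, but a plan that follows the Section 16 sentence would carry the same measure forward.

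**Conclusion.** The point holds in a limited form. The only tetanus-specific analysis in Section 16 is a proportion in which subjects positive at baseline cannot count, so it registers neither reversion nor a falling titer. The Synopsis states a different measure that could register reversion, if tabulated by visit and arm. The general laboratory shift analysis does not clearly fill the gap.

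The size depends on inputs that the protocol does not give. At an assumed seropositivity of 50% to 95%, the measure leaves out half to nearly all of each group. The detectable ratios depend on the assumed SD, and those for the every-other-week arms should not be read across to the monthly arms, which have about 32 subjects after dropout.

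This is a descriptive safety summary and does not touch the ACR50 comparison. It merits correction because the titers are already planned and the stated summary makes little use of them.

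**What to change.** - In Section 16.2.5.2, keep *developed* for ANA only and give tetanus its own sentence.
- For tetanus, report change from baseline in log titer at Week 14 by arm, as a geometric mean ratio versus placebo with 95% CI.
- Add the proportion of baseline-positive subjects who fall below the laboratory's cut-off at Week 14, by arm, and state that cut-off.
- Summarise Week 26 descriptively only. Under Section 7.2, subjects who enter the extension study finish at Week 14, so Week 26 titers come from a self-selected subset of unknown size and do not give a comparison as randomized.
- Reword the Synopsis bullet to match.

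The cost is two sentences and one table. No sample, visit or assay is added.
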